### Procedure

After informed consent is obtained and participants are eligible, they will complete the web-based baseline assessment (approximately 35 minutes) containing demographic questions as well as questions relating to their general health, current mental health, pain experience, and everyday thoughts and behaviors. At the end of the survey, participants will select their preferred days for training, which will be either (1) Monday and Thursday or (2) Tuesday and Friday. Participants will also be asked to provide an email address so that the research team can send links to the training sessions. Participants will then be randomized into 1 of the 3 groups and be invited by email to start their first training session. This email will include a weblink to the appropriate version of the intervention, as well as instructions on how to download the program.

Training sessions will be performed on the web at the participants’ time and place of convenience (using their own computers), twice a week on a separate pair of days (Monday and Thursday or Tuesday and Friday) for 3 consecutive weeks, totaling 6 sessions. This dosage is based on previous pain ABMT literature, which has shown positive training effects for dosages ranging between 4 and 8 sessions [4,7,8]. It is anticipated that the first and final sessions will take approximately 30 minutes, as it includes cognitive assessment measures, whereas sessions 2 to 5 will take approximately 15 minutes to complete. Participants will be asked to complete the sessions during normal waking hours and within 24 hours of receiving a web link. Each session will start with the same instructions, similar to those of previous research [10], and highlight the need to create a quiet and private environment free from distractions for at least 30 minutes. In total, the participants will be sent 6 session links. Necessary reminders will be sent via email and SMS text messages throughout the study.

After each training session, participants will be asked to rate their experience with the task (<2 minutes). Immediately after completion of the final training session, participants will be invited to the postassessment (approximately 15 minutes), with questions relating to their experience of pain, mood, and other relevant psychological experiences associated with their pain. Finally, 1 month after the end of the training sessions, all participants will receive an email invitation for the follow-up assessment (approximately 10 minutes), with similar questions to that of the postassessment (see *Outcomes and Measures* section for further details).

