### Randomization, Allocation Concealment, and Blinding

Participants fulfilling eligibility criteria and willing to participate in this study will be randomly allocated to 1 of the 3 training conditions after the baseline assessment. Randomization will be performed before participants are enrolled by an independent person blinded to all processes within the intervention, using a computerized random number generator. A block randomization technique will be used, allowing 6 participants at a time to be randomized in equal proportions to the 3 training arms. The allocation numbers will be stored on a password-protected university database maintained by the same independent person and will be revealed after participants are enrolled and baseline assessments are completed.

Each time a participant completes the baseline survey, an automatic email will be sent to the principal researcher ([name]). After receiving this email, the participant will be allocated to the next number on the list and, consequently, be assigned to a training arm. Researchers and participants will be blinded to group allocation throughout the trial (ie, double-blind study design). Furthermore, as assessments and training will occur on the web, in the absence of the investigators, the outcome data will be blinded. However, it is possible that a researcher could become aware of the participants’ training conditions to support them adequately in the instance of technical problems. However, it is unlikely that this will entail problems of bias allocation or assessment because of the web-based nature of the study.

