Second, to increase the likelihood of the effectiveness of the intervention design and respond to the call for more theory-driven research on gamification in the field of health [15,34,35], the implementation of game elements in the ABMT procedure was guided by concepts of self-determination theory [36,37] and self-regulation [38]. According to self-determination theory [36,37], which is a well-established theoretical framework within gamification research [34], competence (ie, feeling effective), relatedness (ie, feeling connected to others), and autonomy (ie, feeling a sense of freedom) are the 3 basic psychological needs that determine intrinsic motivation, sustained engagement, and psychological well-being. Previous research has shown that these needs can be addressed by specific elements such as badges, leaderboards, performance graphs, and social competition [39-41]. Another construct that is fundamental to the success of health-related interventions is self-regulation, defined as a dynamic motivational process of setting, pursuing, and maintaining personal goals [42-44]. Self-regulation techniques such as goal setting and self-monitoring can motivate users to engage and sustain in activities, and there is evidence that these techniques can be facilitated in gamification through a range of features such as rewards, goals, levels, and progress bars [45-47].

On the basis of theoretical considerations and the empirical findings discussed in the previous sections, a combination of 5 game elements was incorporated in the gamified task to keep participants motivated and engaged in the sustained and repeated use of the ABMT procedure. The 5 gamification features are briefly described as follows:

Clear gamified goal: At the start of each training session, a clear gamified performance goal will be set for the task to earn as many points as possible and receive badges along the way. Goals that are specific and reasonably challenging are the most effective at increasing motivation and task performance [48] and are likely to increase the satisfaction of the need for competence [40].Feedback loops: During the practice phase, immediate gamified feedback will be provided to help facilitate self-monitoring [46,49] and feelings of competence [40]. For each correct practice trial, the word *Correct!* and a smiling emoticon will appear on the screen, whereas the word

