#### Cognitive Measures

To determine changes in attentional bias and interpretation bias in the different training groups, multilevel modeling analyses will be conducted. For each model, the time point (level 1 unit) will be nested within participants (level 2 units). The variable time for each cognitive measure will have 2 levels (ie, pre- and posttraining), with pretraining as the reference point. The control group (control ABMT) will serve as a reference group for comparisons between the groups over time. A model-building procedure [84] will be used to build the most parsimonious model to test the hypotheses, using the AIC to identify the most appropriate model. All models will be computed using maximum likelihood estimation. In addition, Pearson correlations will assess the relationship between changes in attentional bias magnitude from pre- to posttraining and changes in scores on symptom measures (ie, pain intensity, pain interference, anxiety, and depression).

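### The cognitive pretest listed as Baseline is first taken in session 1, after randomisation, although the article says allocation follows the baseline assessments

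*Protocol article*

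**What the plan says.** All references are to the protocol article.

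- **Randomization, Allocation Concealment, and Blinding.** The allocation numbers "will be revealed after participants are enrolled and baseline assessments are completed". The trigger is the survey: "Each time a participant completes the baseline survey, an automatic email will be sent to the principal researcher". The participant then takes the next number on the list.
- **Procedure, before allocation.** The baseline assessment, about 35 minutes, is described as "containing demographic questions as well as questions relating to their general health, current mental health, pain experience, and everyday thoughts and behaviors". No task is listed.
- **Procedure, allocation and after.** "Participants will then be randomized into 1 of the 3 groups and be invited by email to start their first training session". On that invitation: "This email will include a weblink to the appropriate version of the intervention, as well as instructions on how to download the program".
- **Procedure, session length.** "It is anticipated that the first and final sessions will take approximately 30 minutes, as it includes cognitive assessment measures". Sessions 2 to 5 are put at about 15 minutes.
- **Outcomes and Measures.** Tasks run in Inquisit and questionnaires in Qualtrics. Table 1 ticks both the dot-probe task and the interpretation-bias task under Baseline and Posttraining.
- **Gamified ABMT.** "At the start of each training session, a clear gamified performance goal will be set for the task".
- **Cognitive Measures (Statistical Methods).** Attentional bias and interpretation bias are modelled at two time points, "with pretraining as the reference point". The pre-to-post change in attentional bias is also correlated with change in the symptom measures.

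**The concern.** A baseline is useful in a randomised comparison because allocation cannot have influenced it. The article promises that order, but its own procedure breaks it for the cognitive tests. The score that anchors the two cognitive models and the bias-change correlations is taken once the participant has an arm, through that arm's link.

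Two things are at stake. First, if the gamified version shows its points-and-badges goal before the test, the pretest is no longer free of the intervention, and an arm difference in change could be partly made or masked there. Second, whether the software installs and runs on the participant's own computer is learned only after randomisation. The Statistical Methods overview analyses only randomised participants who complete a session, so an installation failure becomes an exclusion after randomisation.

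**Working it through.** **1. Order of events, from the sections quoted above**

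1. Consent, screening, then the baseline survey of questions (about 35 minutes).
2. Survey completion triggers allocation.
3. The participant receives the arm-specific link and the download instructions.
4. Session 1 (about 30 minutes) contains the cognitive tests.
5. Sessions 2 to 5 (about 15 minutes each) do not.
6. Session 6 (about 30 minutes) contains them again.

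The dot-probe task runs in Inquisit, and the article first has participants download the program at step 3. Its first measurement therefore falls after allocation. The allocation statement and the Baseline tick in Table 1 cannot both stand beside this sequence.

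For the interpretation task the placement is an inference. It rests on the plural in the session-length sentence, on the use of Inquisit for tasks, and on the Cognitive Measures section, which groups the two biases. The survey's mention of everyday thoughts leaves slight room for another reading.

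**2. Does the timing fit?**

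Inputs: a training session has 17 practice and 272 training trials and lasts about 15 minutes (Nongamified Standard ABMT; I assume the practice block is inside the 15 minutes). The attentional-bias assessment has 17 practice and 136 test trials (Measure of Attentional Bias for Pain).

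- Pace: 15 / (17 + 272) = 15 / 289 = 0.0519 minutes per trial.
- Dot-probe assessment: (17 + 136) × 0.0519 = 153 × 0.0519 = about 7.9 minutes.
- Extra time in sessions 1 and 6: 30 − 15 = 15 minutes.
- Left for the interpretation task: 15 − 7.9 = about 7.1 minutes.

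The extra time is compatible with both tasks sitting inside sessions 1 and 6. The article gives no duration for the interpretation task, so the 30 minutes cannot be fully rebuilt.

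**3. How an arm effect on the pretest would pass through**

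The bias index is B = mean RT(incongruent) − mean RT(congruent).

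- If a game goal changes all reaction times by the same amount s: (RT(incongruent) + s) − (RT(congruent) + s) = B. The shift cancels, apart from trials that cross the 200 and 1000 millisecond cut-offs.
- If game framing shifts the index itself by d1 at session 1 and d6 at session 6, the observed change in the gamified arm is (B6 + d6) − (B1 + d1) = (B6 − B1) + (d6 − d1).

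The distortion of change is therefore d6 − d1. It is zero if the tests precede all arm-specific content (d1 = d6 = 0) or if framing acts equally at both sessions (d1 = d6). It remains only if framing alters the index itself, and does so differently in the first and last session. The article gives no figure for d1 or d6.

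**The case against.** The strongest reply is that this is a loose label with little consequence. The Cognitive Measures section says pretraining, not baseline. The assessment is a standard dot-probe with its own word set and practice block. Game elements are described as a layer on the training task, and the Procedure section says that sessions open with common instructions. Participants are not told of the three conditions, so allocation could act on the pretest only through what they see first. Screen order within a session is detail that an article may leave to the full protocol.

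Most of this stands, and it limits the point. It does not remove the conflict over when the Baseline tests occur relative to allocation, nor the late discovery of installation failure.

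A reader might infer more than the documents support:

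- *That the cognitive comparisons are biased.* The text shows a possible route, not an effect. A pretest shift does not simply carry into change, because the posttest sits in the same program and the goal is set in every gamified session.
- *That the main pain results are compromised.* Pain intensity and interference, like anxiety and depression, are questionnaires listed at Baseline, and the survey precedes allocation.
- *That people who never open session 1 damage the planned analysis by lacking a pretest.* The analysis set already leaves out anyone who completes no session.
- *That both cognitive measures are certainly post-randomisation.* This is firm for the dot-probe only.

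One further objection shapes the fix. Moving only the pretest to a neutral script, with the posttest still under game framing, would create a mismatch in the gamified arm alone.

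**Conclusion.** The point holds in limited form. The dot-probe reference score, and probably the interpretation-bias one, is post-randomisation, while the allocation statement and Table 1 together present it as a pre-allocation baseline. This concerns two secondary outcomes and the correlations with symptom change. No sample size, power or significance level is affected.

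The size of any bias is d6 − d1, which is unknown and probably small. That judgement assumes that the tests come early in session 1, as the word pretraining suggests, and that any framing effect is either uniform in speed or similar at the two sessions. The article does not settle either assumption. The change is still worth making: it is cheap, it delivers the order that the article already promises, and it keeps installation failures out of the randomised set. The article gives no installation-failure rate, so that gain cannot be quantified.

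**What to change.** **Participants not yet enrolled.** Run the Inquisit installation and both pretraining cognitive tasks through one common arm-neutral script before allocation, and move the allocation trigger from survey completion to completion of those tasks. Give the posttest with the same script, free of game content, so that testing conditions match.

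**Participants already enrolled.** Verify from the program that the tests came before any arm-specific screen, and report the answer. Label the time point 'pretraining, post-randomisation, session 1' in Table 1, and limit the statement about when allocation is revealed to the baseline survey. Confirm at the same time where the interpretation task was given.

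**Cost.** One shared script and a moved trigger. The baseline step grows from about 35 to 35 + 15 = 50 minutes and session 1 shrinks from about 30 to 15, so the total stays at 65 minutes. Some people may leave during the longer baseline step, but before randomisation, where their loss does not unbalance the arms. Recruitment was under way when the article was written, so two pretest procedures would coexist. Record which one each participant had, and report the change to the ethics committees and the registry, as the article already provides for modifications.

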### Study Program

#### Overview

Participants will be involved in the trial for approximately 2 months, including a 3-week intervention period in which they will be randomized to 1 of the 3 training arms, followed by a 1-month follow-up period. Several strategies will be used to maximize participant retention and follow-up completion. First, we will adopt a web-based completion mode for the surveys and training sessions. Second, participants will receive a personalized email invitation for each training session. These emails will also provide participants the opportunity to ask the research team about any technical difficulties or other obstacles encountered while using the software. Third, we will use a combination of SMS text message and email message reminders according to the participants’ preferences. These reminders will be sent to the participants who do not complete the scheduled session within 24 hours of receiving the weblink. When there is no reaction to the training sessions and reminders after 2 weeks (ie, after 4 training sessions and 4 reminders), the participant will be considered as a dropout. Similarly, participants who fail to complete the follow-up assessments will receive up to 2 emails or SMS text message reminders: one after 24 hours and another one after 48 hours. Finally, the gamified ABMT intervention was developed using gamification features to encourage participants to keep using the program. No incentives will be provided to the participants.

Participant care (eg, rehabilitation program, exercise, cognitive behavioral therapy, and pain medications) concomitant with the ABMT (ie, control ABMT, standard ABMT, or gamified ABMT) will be permitted during the trial. It will be monitored through a *pain-treatment* question that will probe participants’ pain treatments and frequency since the commencement of the study or previous assessment.

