### Statistical Methods

#### Overview

Statistical analyses will be conducted after data collection is completed using the SPSS version 27.0 or later (IBM Corp). Continuous data will be presented as means and SDs, whereas categorical data will be presented as frequencies and percentages. Analyses will follow the intention-to-treat principle and will include all randomized participants who successfully complete at least one training session (ie, minimum threshold exposure to ABMT). To determine whether there are any pretraining differences between the training conditions on demographic variables and baseline characteristics, a series of analyses will be performed. The rates of and reasons for missing data will be reported. To manage missing data, the study will attempt to follow-up on all randomized participants (even if they withdraw from the trial) and, where appropriate, use multilevel modeling for repeated measure data analyses as it allows the incorporation of all available data. Significance for all statistical tests will be set at *P*<.05 (2-tailed). Effect sizes will be presented by its most appropriate effect size (and 95% CI), as described by Lakens [82], with a preference for Cohen *d* where possible [83]. No interim analyses of the trial outcome data are planned.

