#### Symptom Measures

To determine symptom changes (ie, pain intensity, pain interference, anxiety, and depression) in the different training conditions, multilevel modeling analyses will be conducted. For each model, the time point (level 1 units) will be nested within participants (level 2 units). The variable time for each symptom measure will have 3 levels (ie, pretraining, posttraining, and 1-month follow-up), with pretraining as the reference point. The control group (control ABMT) will serve as a reference group for comparisons between the groups over time. A model-building procedure [84] will be used to build the most parsimonious model to test the hypotheses, using the Akaike information criterion (AIC) to identify the most appropriate model. All models will be computed using maximum likelihood estimation.

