#### Engagement Measures

To examine changes in task-related engagement in different training conditions, a multilevel modeling analysis will be conducted. The time point (level 1 units) will be nested within participants (level 2 units). The variable time will have 6 levels (ie, after sessions 1, 2, 3, 4, 5, and 6). A model-building procedure [84] will be used to build the most parsimonious model to test the hypotheses, using the AIC to identify the most appropriate model. The model will be computed using maximum likelihood estimation. To analyze the impact of gamification on interest and enjoyment, a 1-way analysis of variance will be performed. Missing values will be handled using multiple imputations.

Regarding behavioral engagement, Kaplan-Meier survival curves [85] will be calculated to assess the time at which attrition occurred in each training condition and compared statistically using a log-rank test. Participants will be classified as noncompleters if they do not complete all 6 training sessions. Finally, a 1-way analysis of variance will be performed to determine whether there are differences in the mean number of sessions completed between the training conditions.

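### The only described invitation to the posttraining assessment depends on finishing the last session, which does not fit the commitment to follow up every randomized participant

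*Protocol article*

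**What the plan says.** In the protocol article, the Procedure section gives the timing of both later assessments. For the posttraining one: "Immediately after completion of the final training session, participants will be invited to the postassessment (approximately 15 minutes"). For the later one: "1 month after the end of the training sessions, all participants will receive an email invitation for the follow-up assessment". The first is conditional on finishing training; the second is addressed to everyone.

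The Statistical Methods overview states that "the study will attempt to follow-up on all randomized participants (even if they withdraw from the trial"), and that the analyses "will include all randomized participants who successfully complete at least one training session". A person who stops after any of sessions 1 to 5 therefore belongs to the analysis set.

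The Study Program overview deals with nonresponse during training: "When there is no reaction to the training sessions and reminders after 2 weeks (ie, after 4 training sessions and 4 reminders), the participant will" count as a dropout. It does not say whether that person is still sent the posttraining assessment. On reminders it says that "participants who fail to complete the follow-up assessments will receive up to 2 emails or SMS text message reminders", at 24 and 48 hours.

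Table 1 lists pain intensity and pain interference as primary at baseline, posttraining and 1 month. It lists the Intrinsic Motivation Inventory (IMI) interest and enjoyment subscale, also primary, at posttraining only.

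**The concern.** The commitment to follow everyone and the described trigger lead to different data. Staff or an automated system working from the Procedure section would contact only those who finish session 6.

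This matters because finishing training is not a neutral event here. Attrition and session completion are themselves primary outcomes, and Aims and Hypotheses predicts less dropout in the gamified arm. If the posttraining questionnaires reach only those who finish, whether an outcome is observed at that time point depends on engagement and so, if the hypothesis is right, on arm. That time point carries the hypothesis about effects immediately after training. The IMI is the more exposed outcome: with no later measurement, a noncompleter's score would rest wholly on the multiple imputation planned under Engagement Measures.

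**Working it through.** **The statements side by side**

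1. *Who is analyzed.* Randomized participants with at least one completed session (Statistical Methods overview). People who stop after sessions 1 to 5 are in.
2. *Who is modeled at posttraining.* "The variable time for each symptom measure will have 3 levels (ie, pretraining, posttraining, and 1-month follow-up"). Posttraining is one of the three modeled levels for pain intensity, pain interference, anxiety and depression.
3. *Who is invited at posttraining.* As described, those who complete the final session (Procedure).
4. *Who is invited at 1 month.* All participants (Procedure).
5. *Who is to be followed.* All randomized participants, including those who withdraw (Statistical Methods overview).

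Items 1, 2 and 5 call for posttraining data from people whom item 3 does not reach. Item 4 shows that the authors addressed a survey to everyone where they meant to.

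**Can the number affected be derived?** No. The nearest figure is the dropout of about 30% in Sample Size Estimation: 120 × 0.30 = 36 participants, or 12 of 40 per arm. That figure rests on attrition in earlier chronic pain treatment trials and on the 1-month measurement, so it describes overall loss. It is neither a forecast nor a bound for failure to finish session 6. Some of those lost would finish training first, and some who miss session 6 may still answer at 1 month. The analysis definition does not supply the number either: "Participants will be classified as noncompleters if they do not complete all 6 training sessions". Someone who skips session 3 but does session 6 is a noncompleter who is still invited.

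**Scale of a possible shift.** All inputs here are assumptions. Let *p* be the proportion of an arm that stops before session 6, and *g* the gap in SD by which stoppers do worse than completers. If the arm's overall mean is μ, the completers' mean is μ + *p* × *g*. With no true difference between arms, the completers-only contrast (gamified minus control, higher being better) is

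(*p* gamified − *p* control) × *g*

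- 30% in both arms: (0.30 − 0.30) × *g* = 0 for any *g*.
- 35% control, 25% gamified: −0.10 × 0.25 = −0.025 SD; −0.10 × 0.5 = −0.05 SD.
- 40% control, 20% gamified: −0.20 × 0.25 = −0.05 SD; −0.20 × 0.5 = −0.10 SD.

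On these assumptions the shift works against the gamified arm, because the control arm loses more of its poorer responders.

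**The case against.** The Procedure section may describe only the usual path of someone who finishes training, with the Statistical Methods overview giving the rule for everyone else. Nothing in the article bars noncompleters from the posttraining survey. The Study Design section schedules assessment immediately after training for all conditions, and the planned reminders for follow-up assessments, in the plural, may already cover it. A reader might infer that people who stop training are never asked for their posttraining outcomes; the text does not say so. This part of the objection stands: the exact statement is that no invitation to them is described. It does not remove the need to reconcile the two sections, because the only stated trigger excludes people whom the commitment includes.

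A reader might also infer that 36 of 120 participants would lack posttraining data by design, or that the trial's result would be biased by 0.10 SD. Neither is supported. The 36 comes from overall attrition. The 0.10 SD is the largest of several values from assumed inputs, and it describes a completers-only contrast that the plan does not use for pain. The plan specifies maximum-likelihood multilevel models on all available data, and the 1-month pain outcomes are requested from everyone. Under missing at random this mitigates the problem for the pain outcomes, but it does not supply the measurement immediately after training.

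For the IMI, it is tempting to say that imputation would fall on exactly those who disliked the task most. The document does not establish that: it also expects technical difficulties and other obstacles. Engagement is rated after every session, so those ratings could inform the imputation. They do not replace the scale itself.

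**Conclusion.** The point holds as an inconsistency between a stated procedure and a stated commitment, confined to the posttraining time point. It is more than an omitted detail, because the one described trigger is itself an engagement outcome expected to differ by arm, and because primary outcomes are collected at that time. The IMI is the most exposed, having no later measurement; pain intensity and interference are partly protected by the 1-month survey and the multilevel model, as far as missing at random holds.

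No figure in the article changes. The number affected is unknown, and the 0 to 0.10 SD range depends wholly on the assumed stopping rates and on the assumed gap between stoppers and completers. It shows the order of a completers-only shift and does not estimate bias in the planned analysis. Attrition and session completion are unaffected.

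**What to change.** Reconcile the Procedure section with the Statistical Methods overview. Invite every randomized participant to the posttraining assessment on completion of session 6 or, for those who have not completed it, at the end of the training window, whatever the number of sessions done. Keeping the completion trigger for finishers matters: one fixed date for everyone could reach late finishers before their last session. State that the 24- and 48-hour reminders apply to this assessment, and stop contact only on withdrawal of consent.

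Make the IMI available outside the final Inquisit session. Outcomes and Measures says self-reported engagement is administered in Inquisit, so a Qualtrics link alone would not deliver it.

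The cost is a scheduled invitation, another way of delivering the IMI, and one more survey request to noncompleters, whose posttraining measurement would be timed by calendar. The survey link would not recover posttraining attentional bias, because the cognitive assessment sits in the final session. The article reports recruitment as ongoing, so the change could still help participants who had not yet reached that point.
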